### Analytic Plan

To reduce bias, analyses will involve an intention-to-treat design. Linear mixed models will be used to test within-group changes over time and to compare changes between the treatment and control groups in outcomes of interest. The LASSO (least absolute shrinkage and selection operator [56,57]) variable selection technique will be used to find the optional selection of covariates for the final model. Exploration of mechanisms of change variables involves a procedure described by Hayes [58] that uses bootstrapping to test indirect effects. Statistical analysis will be conducted using Stata 15 SE. Although this trial is not fully powered for mediation analysis, findings from these analyses will inform future research to identify mechanisms of change.

We will use a pragmatic approach involving inductive and deductive coding for qualitative data. Qualitative analysis of the interview data collected from the completed single-group feasibility study is underway, and a codebook will be created during the process. The codebook from the single group study will serve as a framework for us to code the qualitative data collected from the pilot RCT. The codebook will be iteratively refined by reviewing the data and themes several times. Qualitative analysis will be conducted using Dedoose, a web app for mixed methods research.

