### Measures

All measures are presented in Table 1. The primary clinical outcome in the study will be depressive symptoms as measured by the PHQ-9. The PHQ-9 is widely used in clinical research and has been used to evaluate older adults with medical and psychiatric illnesses in and outside of health care settings [43,44]. The PHQ-9 has been found to perform comparably to the Geriatric Depression Scale in identifying depression in older adults [45]. Scores on the PHQ-9 can range from 0 to 27 and indicate minimal, mild, moderate, moderately severe, or severe depression symptom severity. Sample items include “In the last week, have you had little interest or pleasure in doing things?” and “In the last two weeks, have you been feeling down, depressed, or hopeless?” Respondents indicate answers on a 4-point Likert scale ranging from “not at all” to “nearly every day.” In primary care patients, the measure has a sensitivity of 88% and a specificity of 88% [43]. The PHQ-9 will be administered at initial screening, baseline, after intervention, and 20-week follow-up. In addition, participants will complete a PHQ-9 self-assessment built into the web-based sessions every other week. To mimic the additional assessment patterns in the treatment group, participants in the control condition will also be administered the PHQ-9 every other week via phone during the 10-week waiting period.

**Table 1 table1:** Study measures and time points.

Variable	Assessment or activity	Screening	Baseline	Postrandomization			Follow-up
				Biweekly	Post		
Depression	PHQ-9^a^	✓	✓	✓	✓	✓	
Anxiety	GAD-7^b^		✓		✓	✓	
Social isolation	PROMIS-SI 8a^c^		✓		✓	✓	
Health self-assessment	PROMIS-GH^d^		✓		✓	✓	
Well-being and quality of life	EQ-5D-5L		✓		✓	✓	
Skill acquisition	CBTSQ^e^		✓		✓	✓	
Acceptability	Modified TEI^f^				✓		
Adherence	Session completion				✓		
Participant background	Sociodemographic, health status, and physical functioning	✓	✓				

^a^PHQ-9: Patient Health Questionnaire-9.

^b^GAD-7: Generalized Anxiety Disorder-7.

^c^PROMIS-SI 8a: Patient-Reported Outcomes Measurement Information System–Social Isolation 8a.

^d^PROMIS-GH: Patient-Reported Outcomes Measurement Information System–General Health.

^e^CBTSQ: Cognitive-Behavioral Therapy Skills Questionnaire.

^f^TEI: Treatment Evaluation Inventory.

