### Sample Size

A sample size of 70 (n=35 per group) should provide at least 80% power, allowing for a 20% attrition rate for both arms. Specifically, we considered the case where the 2 arms are compared in terms of weekly changes in the mean PHQ-9 survey responses between the baseline, 5 interim in-app PHQ-9 assessments (roughly at weeks 1, 3, 5, 7, and 9), and the 10-week follow-up PHQ-9 survey. We assume that the changes in the mean response can be expressed in terms of a linear trend, and the treatment effect can be expressed in terms of the difference in slopes or rate of change (δ = –0.8 × 5 in the total PHQ-9 score over 10 weeks; 5 is the SD in the change scores in our feasibility study). Sample size estimates used the following inputs: (1) type I error rate (α)=.05; (2) the smallest meaningful difference to be detected (δ) over the 10 weeks; (3) power (γ)=.80; (4) we assumed that outcome within-subject variance (σ^2^=6^2^; estimated from our feasibility study data) is constant over time; (5) the number of repeated measurements per person (n): 1 baseline, 5 in-app assessments, 1 final postbaseline for a total of 7 repeated assessments; and (6) regarding between-subject variation of the slopes, we assumed a variance of random slopes τ^2^=0.2 (estimated from our feasibility study data). The sample size is 52 for both arms with equal randomization probabilities; with an attrition rate of 20% for both arms, the total required sample size is 65. We set the final target sample size to 70 to allow room for higher attrition and lower adherence.

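### The efficacy model's covariates are left to LASSO and none is fixed, so the primary estimate depends on data-driven selection and adjustment for baseline PHQ-9 is not guaranteed

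*Protocol article*

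**What the plan says.** The Analytic Plan uses linear mixed models to test within-group change and to "compare changes between the treatment and control groups in outcomes of interest". The next sentence hands the covariates to LASSO: the "variable selection technique will be used to find the optional selection of covariates for the final model". No covariate is named as fixed. The article does not list the candidates, and it does not say which data drive the selection. The trial's own data is the natural reading, but it is not stated.

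The Sample Size section describes the data more closely. The repeated measures are "1 baseline, 5 in-app assessments, 1 final postbaseline for a total of 7 repeated assessments", and "the treatment effect can be expressed in terms of the difference in slopes or rate of change". Baseline PHQ-9 is thus part of the response there, not a covariate. It is available for everyone at no extra cost: "The PHQ-9 will be administered at initial screening, baseline, after intervention, and 20-week follow-up".

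**The concern.** Randomisation already deals with confounding, so covariates in the efficacy model serve precision. Choosing them by an algorithm in a small sample has two drawbacks. First, the estimate depends on what happens to be selected, and ordinary standard errors from the refitted model ignore that step. Second, the baseline value of the outcome, the obvious adjustment variable in a depression trial, is not guaranteed a place.

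At stake is whether the effect estimate and its standard error can be taken at face value. The Objective section gives evaluating efficacy as the primary aim, the trial is sized for 80% power, and the results are meant to inform a larger trial.

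**Working it through.** **Inputs from the Sample Size section.** "type I error rate (α)=.05" (taken as two-sided; the article does not say); "power (γ)=.80"; "δ = –0.8 × 5 in the total PHQ-9 score over 10 weeks; 5 is the SD in the change scores in our feasibility study", i.e. 4 points over 10 weeks or 0.4 per week; residual variance σ² printed as 6² = 36; random-slope variance τ² = 0.2; measurements at weeks 0, 1, 3, 5, 7, 9 and 10 (mean 5, sum of squares Sxx = 90). Completers: 70 × 0.8 = 56, or 28 per arm.

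**Step 1. The plan's own figure (52 in total).** For a slope difference, n per arm = 2(1.960 + 0.842)²(σ²/Sxx + τ²)/0.4².
- σ² = 36: 2 × 7.849 × 0.6/0.16 = 58.9 per arm, 118 in total.
- σ² = 6: 2 × 7.849 × 0.2667/0.16 = 26.2 per arm, 52.3 in total.

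The stated 52 follows from σ² = 6, not from 36 as printed. That is a separate matter, but because of it both values are carried below.

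**Step 2. Slope model without a baseline constraint, 28 per arm.** SE = √[2(σ²/Sxx + τ²)/28]; power = Φ(0.4/SE − 1.96).
- σ² = 6: SE = √(0.5333/28) = 0.138; power 82.6%.
- σ² = 36: SE = √(1.2/28) = 0.207; power 48.9%.

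**Step 3. Same model with one baseline mean for both arms.** Fixed effects are intercept, time and arm-by-time, with no arm term at week 0. The variance comes from generalised least squares with random intercept and slope. The intercept variance and the intercept-slope correlation are not in the article; 4 to 25 and −0.3 to 0.3 are assumed.

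| σ² | Unconstrained | Common baseline mean |
|---|---|---|
| 6 | 82.6% | 82.7% to 90.3% |
| 36 | 48.9% | 51.9% to 73.9% |

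The gain is largest at intercept variance 4 and correlation −0.3. With σ² = 6 and correlation 0.3 it is close to nil. It is never negative, because the constraint removes a parameter that randomisation makes zero.

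**Step 4. Two-point version.** With SD of change 5 and baseline-to-week-10 correlation ρ (not given), the ANCOVA variance is (1 + ρ)/2 times the change-score variance. At 28 per arm (normal approximation) a change-score comparison has Φ(4/(5√(2/28)) − 1.96) = 84.9% power. ANCOVA has 96.0%, 93.3% and 90.1% at ρ = 0.3, 0.5 and 0.7.

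**Step 5. LASSO selection in an ANCOVA-type model.** Simulated with 28 per arm, arm unpenalised, cross-validated penalty, refit by least squares, and an assumed 15 candidates of which only baseline matters.
- Baseline dropped: 36% at ρ = 0.3, 2.5% at 0.5, 0% at 0.7 (400 runs each).
- Power, LASSO against fixed ANCOVA: 95.0% v 95.0%, 92.3% v 92.3%, 86.3% v 87.0%.
- Type I error at ρ = 0.5: 6.8% v 5.0% (1,000 runs, Monte Carlo SE 0.7-0.8 points). Further runs with 15 candidates gave 6.0-7.0%; with 30 candidates, 8.6-9.5%.
- Standard error, in outcome SD units: the naive SE averaged 0.246 against a true SD of the estimate of 0.274, so it is 1 − 0.246/0.274 = 10% too small.

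Nominal power looks unharmed partly because the standard error is understated. With 30 candidates and ρ = 0.65 the estimator's SD was 0.224 against 0.202 for the fixed model, a variance ratio of (0.224/0.202)² = 1.23, although baseline was never dropped.

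**The case against.** Four objections deserve an answer.

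**Baseline is an outcome, not a candidate.** A reader might infer that LASSO can discard baseline PHQ-9 and so cost the trial much of its power. The article does not support that. In the seven-measurement model covariate selection cannot touch the response vector. Even in an ANCOVA-type model, baseline is dropped often only where it carries little information, and the nominal power difference in Step 5 was at most 0.7 points. This objection stands. The precision at issue in Steps 3 and 4 is lost by not constraining or adjusting for baseline, however other covariates are chosen.

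**Treatment could be shrunk out.** A reader might also fear that the arm term is penalised. The article applies LASSO to covariates, and the arm comparison is the stated purpose of the model. Nothing suggests that arm is a candidate, so this is not part of the point.

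**It is a pilot.** The article calls the results preliminary and does not present the model as confirmatory. That lowers the stakes but does not remove them, given the efficacy aim and the formal power calculation.

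**The detail may be in an analysis plan that is not shown.** Candidates, tuning and forced-in terms may well be there, and their absence is not criticised. But the article states a rule, that covariates are chosen by LASSO. Fixing them elsewhere would reverse that rule, not fill it in.

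**Conclusion.** The point holds as a weakness of pre-specification that is worth correcting, not as a demonstrated large loss of power caused by LASSO.

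- If the final model is ANCOVA-type, inference after selection is mildly anti-conservative: type I error about 6-7% with 15 candidates, more with 30. These figures rest on assumed correlations, candidate numbers and tuning, with Monte Carlo error of up to about 1 point. They show direction and order of size only.
- If baseline stays the first repeated outcome, LASSO cannot remove it. Leaving the baseline means free still forgoes between almost nothing and about 8 power points at σ² = 6 (82.6% to at most 90.3%), and 3 to 25 points at σ² = 36 (48.9% to 51.9-73.9%). These ranges rest on the assumed intercept variance and intercept-slope correlation.

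The article does not settle which of the two models is meant, and the same remedy serves both.

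**What to change.** State one primary model for the 10-week comparison and exempt it from data-driven selection. Either of these would do:

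- a linear mixed model with time and arm-by-time, baseline PHQ-9 as the first outcome and its mean constrained equal across arms; or
- a linear mixed model on the post-baseline scores with arm, time, arm-by-time and baseline PHQ-9 as a fixed covariate.

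Keep LASSO for a sensitivity or predictor analysis labelled as such, with the arm terms and baseline PHQ-9 left unpenalised. The cost is a sentence or two in the analysis plan. No new data, visits or participants are needed, since baseline PHQ-9 is already collected in both arms.

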### Ethics Approval

This study was reviewed and approved by the Health Sciences and Behavioral Sciences institutional review board (IRB) at the University of Michigan. Approval was granted on April 19, 2022 (HUM00212950).

A waiver of documentation for written consent was approved by the IRB. Consent to participate in the study will be obtained orally from participants. Consent will be obtained at 2 points. At first contact, participants will provide consent to be screened. Second, after screening and before the baseline interview, study-eligible participants will be asked to provide oral consent to participate in the study. This will be recorded via a tape recorder after a verbal review of an informed consent document. To ensure the quality of consent, all participants will reconsent at the beginning of the first web-based session of the intervention. This will be accomplished by providing a brief written consent document on the first page of the web-based session. Participants must confirm their understanding of the document to proceed to the first web-based session.

The privacy of participants will be protected in several ways. All participants will complete web-based therapy sessions by themselves in their private homes. Direct identifiers are not stored in the web-based program. Mental health assessment data collected as part of the web-based sessions are stored in a HIPAA-compliant database. Other study data (eg, baseline and posttest assessments) are entered and managed on REDCap. Only the study team members directly authorized by the principal investigator will have access to study data with identifiers. Access is typically restricted to the principal investigator and project coordinators. As the study involves follow-up, direct identifiers will be retained for this purpose. After completion of the study and data cleaning, all direct identifiers will be removed from the database, rendering the final data set anonymous.

Those who qualify for the trial will be paid up to US $100 for participation. Compensation is determined based on the number of assessments completed. Partial compensation is available (eg, participants who complete only the baseline assessment will receive US $30). Participants will be provided US $30 for the baseline, US $50 for the posttest, and US $20 for the follow-up. Payment will be provided directly to the participant via mailed check or Visa gift card, whichever is preferred by the participant.

## Results

Funding for this multiphase project was awarded in November 2020. IRB approval for the single-group feasibility study and the proposed RCT was attained in April 2022. Enrollment for the single-group study began in May 2022, and all subjects completed the intervention by December 2022. Recruitment for the RCT began in January 2023, and the study completion is anticipated by December 2023. The trial is registered at ClinicalTrials.gov (NCT05593276).

## Discussion

### Principal Findings

To our knowledge, this is the first RCT of layperson-facilitated iCBT for low-income homebound older adults with depression. We hypothesize that the Empower@Home intervention will be feasible and acceptable, reduce depressive symptoms, and improve psychosocial functioning and health-related quality of life. Existing evidence-based mental health treatments are often inaccessible to homebound older adults, who have been largely excluded from digital mental health interventions. This trial addresses that gap by testing an intervention specifically designed to the needs of this population.

iCBT participants are exposed to the same components as conventional CBT, though they receive psychoeducational materials through a self-directed internet platform. A meta-analysis of iCBT trials with older adults found a large pooled within-group effect size, although most studies adopted weak designs [24]. In a recent iCBT pilot trial led by the last author, homebound older adults with low computer literacy found that iCBT was an acceptable way of treating depression and resulted in significant reductions in depressive symptoms at the posttest [33]. A recent RCT showed that iCBT also effectively prevented depression among older adults with multiple chronic conditions [29].

As a result of the COVID-19 pandemic, virtual care is gaining rapid traction, which provides unprecedented opportunities for integrating digital mental health interventions into community aging services. The COVID-19 pandemic has accelerated the adoption of technology and virtual care in community settings, which is likely to stay after the pandemic. Although notable age differences in technology use remain, the adoption of key technologies by older adults has grown markedly, and the age-related digital divide continues to narrow. For example, smartphone ownership increased from 46% in 2018 to 61% in 2021 among those 65 years and older [59]. Given the increased focus on digital inclusion, there is likely to be continued growth in access to broadband internet. The Affordable Connectivity Program (formerly Emergency Broadband Benefit), a long-term, US $14 billion program authorized by the 2021 Infrastructure Investment and Jobs Act, provides up to US $30 per month toward internet service and up to US $100 to purchase a computer or tablet device for eligible households. With providers and clients more willing to use technology, increased funding, regulatory changes, and improved technology infrastructure, digital mental health interventions are ripe for implementation in community aging services, where many homebound older adults receive services.

The pilot RCT will provide crucial data for a fully-powered effectiveness trial in the future. If confirmed effective, several probable funding mechanisms can facilitate long-term sustainability. These funding sources include Medicaid, federal grants, private pay, and commercial insurance. For example, community agencies can apply for federal grants authorized by the Older Americans Act that support community-based health-promotion programs. Many commercial insurance providers are already reimbursing for iCBT services [60,61]. Agencies could also charge a sliding scale fee to cover operating costs and raise revenues. In terms of training, most of the provider training materials are web-based, making it relatively easy to scale up.

### Strengths and Limitations

The strengths of this study include an iteratively developed intervention incorporating patient and provider feedback, randomized design, use of laypersons as interventionists, and recruitment of an underserved, hard-to-reach population with high unmet mental health needs. For limitations, this study uses a small sample size and a waitlist control design, which may lead to an overestimation of treatment effects [62]. Though this intervention is intended to address depression in older adults, it may also address related conditions not measured in this study, such as demoralization [63,64].

### Conclusions

The planned study addresses the shortage of iCBT products suitable for homebound older adults. Our treatment innovation, if found effective, will contribute to closing the digital divide and mental health disparities in homebound older adults. Study implications extend to other digital mental health interventions and populations with physical disabilities and access restrictions who face persistent disparities in mental health.

## Abbreviations

CBT: cognitive behavioral therapy
HIPAA: Health Insurance Portability and Accountability Act
iCBT: internet-delivered cognitive behavioral therapy
IRB: institutional review board
PHQ-9: Patient Health Questionnaire-9
PROMIS-GH: Patient-Reported Outcomes Measurement Information System–General Health
PROMIS-SI: Patient-Reported Outcomes Measurement Information System–Social Isolation
RCT: randomized controlled trial
